##### Clinical reaction time

At every time point, both athletes with mTBI and matched control athletes will perform the Clinical Reaction Time test (RT_clin_). RT_clin_ is a clinical test measuring simple reaction time using an 80-cm dowel with one end inserted in the middle of a hockey puck (Eckner et al., 2010). The participants will sit with their dominant arm on a table, leaving their wrist and hand off the side of the table. The investigator then brings the hockey puck to the level of the athlete's first finger and thumb. After a random duration between 2 and 5 s, the investigator releases the dowel, and the participant attempts to catch the dowel as soon as possible. The distance from the superior aspect of the hockey puck to the superior aspect of the participant's hand is measured. For the present study, two practice trials followed by eight measured trials will be completed by athletes at each assessment.

##### Instrumented BESS

Quiet standing balance will be assessed at every time point using the BESS (Bell et al., 2011). Both athletes with mTBI and matched control athletes will complete this test wearing five inertial measurement units (APDM Inc., Portland, OR) placed on the sternum, lumbar spine, right shank, and right and left feet. The footwear of the athletes will be recorded, and tests will be video recorded. The full BESS battery involves a double-leg stance, single-leg stance (on non-dominant foot), and tandem stance (nondominant behind dominant) performed on both firm and foam surfaces. Each trial will last 30 s, but errors will only be counted during the first 20 s.

##### Push and release reactive postural response paradigm

Reactive postural responses will be assessed using the Push and Release (P&R) test (Smith et al., 2016; El-Gohary et al., 2017). The P&R is a clinical test that examines reactive postural responses and compensatory stepping behavior after a loss of balance (Jacobs et al., 2006). Prior to each trial, a footplate (8″ long, 5.75″ wide at the toes, 4″ wide at the heels) will be placed on the floor, and the subject will be asked to press their feet firmly and symmetrically against each side of the footplate to ensure a standardized stance width at the beginning of each test. Subjects will lean, while supported by an investigator, until their center of mass is just beyond their base of support (Figure 1, left). After maintaining the supported leaning posture, the investigator will unexpectedly release their hands, requiring the subject to take a step (Figure 1, right). Subjects will perform the P&R, with eyes closed, in four directions: forward, backward, left, and right. Athletes demonstrate faster auditory and visual reaction times than healthy controls (Kaur et al., 2006) and typically perform better on balance tests than nonathletes (Davlin, 2004). Therefore, to increase difficulty of the P&R task for an athletic population, participants will be asked to close their eyes. During competition, athletes are often required to produce appropriate cognitive and motor responses simultaneously. Dual-task assessments are more sensitive to cognitive and motor impairments after mTBI than single-tasks beyond the acute phase of recovery (Register-Mihalik et al., 2013). Therefore, to make the P&R more functionally relevant and sensitive to cognitive and motor impairments, participants will be tested under single- and dual-task conditions. The dual task will be randomized and consists of serial subtraction by 3's, phonemic verbal fluency (FAS test), categorical verbal fluency (animal or fruit naming), and reciting every other letter of the alphabet (Tombaugh et al., 1999). During the dual-task condition, as soon as participants are in the supported leaning posture, they will be prompted with one of the four cognitive tasks. Participants will respond at least three times before being released unexpectedly by the investigator. Inertial measurement units (APDM Inc.) will be placed on the sternum, lumbar spine, right shank, and right and left feet. One sensor will be placed on the investigator's hand to determine release of support time. Data will be collected at 128 Hz and processed using custom-built algorithms in MATLAB (MathWorks, Natick, MA).

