#### Statistical Analysis

Aim 1 of phase 1: *t* tests will be used to determine if time to stabilization during the P&R differs between healthy subjects and subjects <48 h after concussion. Linear regression models will assess group differences while controlling for potential confounders of age, sex, contact/noncontact sport, and BMI. Concussion history will be recorded and explored as a covariate if necessary. As clinical scores are ordered with three levels, Wilcoxon Mann-Whitney *U* tests and generalized linear models for ordered multinomial outcomes (ordinal logistic regression) will compare clinical scores between groups. If the clinical scores exhibit a high ceiling effect, scores will be dichotomized and analyzed using χ^2^ tests and logistic models. *t* tests will assess whether concussed athletes had greater differences between single- and dual-task conditions relative to controls.

Aim 2 of phase 1: Bonferroni-adjusted *t* tests will be used to compare groups PostRTP to determine whether athletes with a recent mTBI take longer to stabilize during reactive postural responses after being medically cleared to RTP. Analogous secondary tests will be used for the PreRTP and 6Month assessments. We will also compute the difference in time to stabilization between assessments (e.g., change from Acute to PostRTP) to determine whether concussed athletes improved their postural responses over time. *t* tests will compare the group differences in the change between assessments. Longitudinal analysis using generalized estimating equations (GEEs) with compound symmetry working covariance models will be used to contrast each outcome of the P&R test at each assessment while controlling for lean direction; single vs. dual task; and possible confounders of age, sex, contact/noncontact sport, and BMI. A group-by-assessment interaction will determine if adjusted group differences changed between assessments. Two- and three-way interactions with task (group × task, group × task × assessment) will be included to test for group-difference in task, and if significant, final models will include these interactions. Ordinal logistic regression in a GEE framework will be used to assess changes in clinical scores between assessments.

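### The GEE models single versus dual task but not which of the four randomized cognitive tasks was performed, so differences between tasks add avoidable residual variance to the dual-task contrasts.

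*Protocol article*

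**What the plan says.** The protocol article, under the heading on the Push and Release paradigm, has every athlete tested in four lean directions: "Subjects will perform the P&R, with eyes closed, in four directions: forward, backward, left, and right". Testing is under single- and dual-task conditions. On the second, the article says "The dual task will be randomized and consists of serial subtraction", and it goes on to name letter fluency, category fluency and alternate-letter recitation as the other three options. On each dual-task trial, participants are told the task after they have taken the supported lean: "they will be prompted with one of the four cognitive tasks". The article does not describe the randomization scheme or give the number of trials per direction.

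The phase 1 Statistical Analysis section tests hypothesis 1b directly: t "tests will assess whether concussed athletes had greater differences between single- and dual-task conditions relative to controls". The longitudinal GEE then contrasts each outcome "while controlling for lean direction; single vs. dual task; and possible confounders of age, sex, contact/noncontact sport, and BMI". It adds interactions: "Two- and three-way interactions with task (group × task, group × task × assessment) will be included to test for group-difference in task". In that section, task means single versus dual. Which cognitive task was performed is not among the listed terms.

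**The concern.** Mental arithmetic, word retrieval and alphabet recitation are different demands. The article's Introduction argues that a concurrent cognitive load limits preparation for a perturbation. On that argument, different loads could plausibly give different stabilization times. Lean direction, the other factor that changes from trial to trial, is in the model, while cognitive task, which is known at the moment of prompting, is not.

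If the tasks differ, an athlete's dual-task average depends partly on which tasks came up. That variation is neither balanced out by any stated design nor removed by the listed model. It falls on the t test for hypothesis 1b and on the group-by-task terms. The Sample Size section gives no power for these contrasts, so no stated margin covers a loss.

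**Working it through.** **The article's own figures.** Two-sample t test, noncentral t, 40 per group:

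- d = 1.7, alpha 0.05: above 99.9% (stated: above 99%).
- d = 0.72, alpha 0.0125: 74.5% (stated: 74%).
- d = 0.72, alpha 0.05: 88.9%, in line with the 88% stated for change between assessments.

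These reproduce, and none of them involves cognitive task.

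**Inputs for the dual-task cost.** From the article: four tasks, four directions, 40 per group. Assumed, because the article gives no figure:

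- four single-task and four dual-task trials per session;
- each dual-task trial's task drawn independently;
- outcome variance of 1 per trial, half of it trial residual;
- task SD *s* of 0.1 to 0.5 outcome SDs;
- variance of athletes' true dual-task cost *c* of 0, 0.10 or 0.25;
- a reference power of 80% at two-sided alpha 0.05, chosen for illustration. It is not a phase 1 figure from the article.

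**Formulas.** An athlete's cost is the dual-task mean minus the single-task mean, so stable differences between athletes cancel.

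- Variance without task noise: 2 × 0.5/4 + *c* = 0.25 + *c*.
- Added by independent task draws: *s*²/4.
- Inflation: F = 1 + (*s*²/4)/(0.25 + *c*).
- The standardized effect giving 80% power, 0.634, is divided by √F.

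| *s* | Added variance | *c* = 0: F, power | *c* = 0.10: F, power | *c* = 0.25: F, power |
|---|---|---|---|---|
| 0.1 | 0.0025 | 1.010, 79.6% | 1.007, 79.7% | 1.005, 79.8% |
| 0.2 | 0.0100 | 1.040, 78.4% | 1.029, 78.9% | 1.020, 79.2% |
| 0.3 | 0.0225 | 1.090, 76.5% | 1.064, 77.5% | 1.045, 78.2% |
| 0.5 | 0.0625 | 1.250, 70.7% | 1.179, 73.3% | 1.125, 75.2% |

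The largest loss is 80 − 70.7 = 9.3 points, and it requires every athlete in a group to have the same true cost. With *c* = 0.25 the range is 0.2 to 4.8 points; with *c* = 0.10 it is 0.3 to 6.7.

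**Without replacement.** If each of the four tasks is used once over four trials, every athlete's dual-task mean contains the same average task effect. Its variance between athletes is then zero under additive effects, and nothing is lost from that mean.

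**A comparison of group means.** If the PostRTP comparison (d = 0.72, alpha 0.0125) were made on a four-trial dual-task mean, with *s* in units of that mean's SD, inflation would be 1 + *s*²/4. Power would go from 74.5% to 74.3% at *s* = 0.1 and to 71.3% at *s* = 0.5. The loss is smaller than for the cost because between-athlete variance stays in the denominator.

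**The case against.** The strongest reply is that an article may leave both the randomization scheme and a nuisance covariate to fuller documents, and that four tasks and four directions fit a random permutation perfectly well. The first half largely stands. A reader might infer that tasks are unbalanced over directions, or that only 4!/4⁴ = 9.4% of sessions would contain each task once. The article supports neither. It says only that the dual task is randomized, and the 9.4% needs independent draws with one trial per direction.

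The reply is weaker on the model. The GEE terms are written out, they include the other trial-level factor, and they omit this one. A better-specified model can be recommended without claiming that anything is contradicted.

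Three further limits are accepted:

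- Randomization makes the task independent of group in expectation, so this is loss of precision and not bias. Single-task results are untouched.
- The between-task SD is unknown. At 0.1 to 0.2 the loss is at most 1.6 points in every column above.
- A reader might carry the argument to phase 2 and expect the hazard ratio to be pulled toward 1. The phase 2 Statistical Analysis section names time to stabilization but specifies no dual-task predictor, so the article gives no basis for that claim.

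**Conclusion.** The point holds as a modest precision improvement for hypothesis 1b and the group-by-task terms. The listed model pools four different cognitive loads into one dual-task level, and the article states no balancing that would make this harmless. Under the assumptions above, the loss from 80% power is below 1 point at a task SD of 0.1. At a task SD of 0.5 it is about 5 points with a true-cost variance of 0.25, about 7 with 0.10, and at most about 9 with none. It is zero for additive effects in an athlete's mean if tasks are drawn without replacement over four trials. No result is shown to be biased and no stated power figure is wrong.

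**What to change.** Record the cognitive task on every dual-task trial. Add it to the GEE as a factor nested within the dual-task level, coded to sum to zero so that the single-versus-dual coefficient remains an average over the four tasks.

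Where this is not already done, assign tasks in a randomized balanced order, each task once over the four directions at a visit, and give the athlete with mTBI and the matched control the same order. This matters because the hypothesis 1b t test has no model term to absorb the task, so it benefits only through the design. If the order is already balanced, one sentence saying so and the model term are enough.

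The cost is a prepared sequence sheet and three model degrees of freedom on trial-level data. No trials or participants are added.

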
**Figure 1 F1:**
[figure not shown]
Push and release test **(A)** Prior to release, the subject's center of mass is beyond the subject's base of support (heels). **(B)** Immediately after release of support. **(C)** Subject recovered using one backward step.

#### Outcome Measures

Raw acceleration and angular velocity data from the five inertial measurement units will be used to calculate the following outcomes from the P&R test (Figure 2): step latency, step length, and time to stabilization.

**Figure 2 F2:**
[figure not shown]
(Left) Support was released at time 0 (solid yellow). Step latency (blue dashed line) and time to stabilization (yellow dashed line) are marked.

Using data from the sensor on the investigator's hand, release of support (*t*_0_) will be identified when acceleration is >5% of gravity. Step latency will be calculated as the amount of time (seconds) from *t*_0_ to first foot movement. First foot movement will be detected when foot acceleration >7% of gravity and rotational rate is >7 degrees/s (El-Gohary et al., 2017). To determine step length (meters) of the first step, the double integral of acceleration of the foot from first foot movement to the next zero velocity instant will be calculated. Magnitude thresholds of 97.4 degrees/s for rotational rate and 0.8 m/s^2^ relative to gravity for acceleration will be used to determine the zero velocity instant (Rebula et al., 2013). Time to stabilization will be calculated as the amount of time (seconds) from *t*_0_ to stabilization. Stabilization will be detected when lumbar acceleration <7% of gravity and rotational rate <7 degrees/s, after the last step (El-Gohary et al., 2017).

The primary outcome measure will be time to stabilization. Secondary outcomes include step latency, step length, and the clinical score (number of steps) (Horak et al., 2009). The clinical score will be rated as follows: 0 = fall, 1 = recovers independently but takes more than 1 step, 2 = recovers independently with one step.

#### Sample Size

The sample size for aim 1 of phase 1 was calculated from differences between symptomatic concussed subjects and healthy controls in response to a tethered pull perturbation (Pan et al., 2015), with an estimated difference of 1.7 standard deviations (Cohen *d* = 1.7) between concussed subjects with residual balance complaints and healthy controls. With an effect size of 1.7, we will have >99% power to detect group differences at acute assessments with a 0.05 significance level and a two-sided *t* test with 40 subjects per group.

The sample size for aim 2 of phase 1 was based on an estimated effect size of Cohen *d* = 0.72 between asymptomatic, previously concussed individuals and healthy controls (Pan et al., 2015). If we observe a similar effect size of 0.72 for the P&R test, we expect 74% power to detect group differences at the primary PostRTP time point using a two-sided *t* test at a Bonferroni-corrected significance level of 0.0125 (0.05/4 for four outcomes: time to stabilization, step latency, step length and clinical score) with 40 subjects per group. Comparisons at PreRTP and 6Month assessments will also be performed but will be considered secondary. We also expect 88% power to detect group differences in the change between acute and subsequent assessments with 40 subjects per group.

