Reactive postural responses are common in athletic competition and essential for athlete safety, but this domain of balance control has not been studied extensively after mTBI. Time to stability after dynamic movement can discriminate between those with history of mTBI and healthy controls (Lynall et al., 2020), suggesting that stability may be an important post-mTBI measure. However, no study has examined reactive postural responses in athletes with mTBI. We suspect the lack of knowledge concerning reactive postural responses after mTBI stems from two sources. First, reactive postural responses have been historically considered reflexive (subcortical) (Jacobs and Horak, 2007; Jacobs, 2014). However, it is likely that reactive postural responses rely on interaction among spinal circuits, the brainstem, and the cortex (Jacobs and Horak, 2007). As the focus of mTBI has traditionally been on cortical damage, postural responses may have been considered too automatic/reflexive to be disrupted by mTBI. The second possible reason for a gap in knowledge is logistical; traditional assessments of postural responses require sophisticated moving platforms (Zettel et al., 2008a,b) or tether-release (MacKey and Robinovitch, 2005; Inness et al., 2015) setups. Given some of the patient burden hurdles ingrained within clinical mTBI research, it is perhaps unsurprising that few studies have examined postural responses using these types of equipment. In fact, in designing this protocol, we considered implementing similarly controlled postural response paradigms (e.g., tether-release, moving platform, etc.). However, the need for a clinically feasible testing paradigm was critical to minimize the burden on student-athlete participants. Therefore, we selected the P&R test, a clinical test traditionally quantified using visual scoring. The notable weakness of this task is the relative simplicity for highly athletic individuals—few athletes should take multiple steps or struggle to recover. The use of wearable sensors is therefore essential and enables quantitative metrics of response latency, step length, and time to stabilization. The combination of wearable inertial sensors with the clinical P&R test facilitates assessments of reactive postural responses within an athletic training room with minimal added burden on the athlete. If we find athletes with recent mTBI take longer to regain stability or exhibit longer step latencies, it will provide evidence that mTBI impairs the reactive restoration of balance, demonstrating that mTBI affects all domains of balance control. Additionally, if we find differences between groups across time, it will support our hypothesis that postural responses are persistently impaired after mTBI. Such findings, coupled with the clinical feasibility of the P&R assessment, may spur the integration of postural response testing into the clinical management for mTBI. In the future, more work will be needed to develop outcome measures with established cutoff values for return-to-to play that could be incorporated into a testing battery.

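### Aim 2 tests its one primary outcome at its one primary time point at 0.0125, an alpha shared equally with three secondary outcomes; this is valid but costs about 14 points of power (74% against 89%)

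*Protocol article*

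**What the plan says.** **Outcomes.** The phase 1 Outcome Measures section ranks them: "The primary outcome measure will be time to stabilization. Secondary outcomes include step latency, step length, and the clinical score".

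**Time point.** The phase 1 Sample Size section names one for aim 2: "we expect 74% power to detect group differences at the primary PostRTP time point". It sets the others below it: "Comparisons at PreRTP and 6Month assessments will also be performed but will be considered secondary".

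**Significance level.** The same section uses 0.0125 for aim 2 and explains it as "0.05/4 for four outcomes: time to stabilization, step latency, step length and clinical score". The inputs are d = 0.72, 40 per group and a two-sided t test. The phase 1 Statistical Analysis section carries the rule into the analysis: the PostRTP comparison of time to stabilization is itself Bonferroni-adjusted.

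**Neighbouring calculations.** Aim 1, on the acute assessment, is powered at 0.05 with d = 1.7. For change over time, Sample Size adds: "We also expect 88% power to detect group differences in the change between acute and subsequent assessments", with 40 per group. It gives neither an alpha nor an effect size for that figure.

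**The concern.** With one primary outcome at one primary time point, aim 2 has one primary test. A single primary test needs no multiplicity correction on account of outcomes ranked below it. The plan still gives each of the three secondary outcomes the same quarter of alpha as the primary. Outcome Measures ranks the four; Sample Size treats them as equals.

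One of those quarters goes to the clinical score. The Discussion expects that "few athletes should take multiple steps or struggle to recover", and Statistical Analysis already provides for a ceiling effect, so this outcome may have little room to separate the groups.

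At stake is the main aim 2 question: whether athletes cleared to return to play still take longer to stabilize. If the true difference is the planning value, the current rule misses it about one time in four; at 0.05 it would be missed about one time in nine.

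**Working it through.** **Inputs, all from the phase 1 Sample Size section:** d = 0.72; n = 40 per group; two-sided two-sample t test; alpha = 0.05/4 = 0.0125.

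**Formula.** Degrees of freedom = 2n − 2 = 78. Noncentrality = d × √(n/2) = 0.72 × √20 = 3.22. Power is the probability that a noncentral t variable with these parameters exceeds the two-sided critical value (the opposite tail is negligible).

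**Step 1: reproduce the plan's figure.** At alpha 0.0125 the critical value is 2.557 and power is 74.5%. The stated 74% reproduces.

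**Step 2: the same test at the full level.** At alpha 0.05 the critical value is 1.991 and power is 88.9%.

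| Two-sided alpha | n per group | Power at d = 0.72 | Chance of missing it |
|---|---|---|---|
| 0.0125 | 40 | 74.5% | 25.5% |
| 0.05 | 40 | 88.9% | 11.1% |
| 0.0125 | 45 | 80.4% | 19.6% |
| 0.0125 | 55 | 88.9% | 11.1% |

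The difference at 40 per group is 88.9 − 74.5 = 14.4 percentage points. Staying at 0.0125, 80% power needs 45 per group, and about 89% needs 55, which is 15 more per group.

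**Step 3: sensitivity to missing visits.** The calculation assumes that all 40 per group are assessed. As assumptions of this review:
- 10% missing (36 per group): 69% at 0.0125, 85% at 0.05.
- 20% missing (32 per group): 62% at 0.0125, 81% at 0.05.

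**Step 4: error control under a hierarchy.** Suppose the primary is tested at 0.05 and the three secondary outcomes by Holm at 0.05 only after it succeeds. If the primary null is true, any false claim requires the primary to be falsely rejected, which has probability at most 5%. If the primary null is false, only the secondary outcomes can give a false claim, and Holm holds that at 5%. The family-wise error of the four PostRTP tests is therefore at most 5%, as under Bonferroni.

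**Step 5: the 88% for change.** Its inputs are not stated, so several were tried with 40 per group:
- d = 0.72 at 0.05 gives 88.9%, which rounds to 89%.
- d = 0.72 at 0.0125 gives 74.5%.
- d = 0.84 at 0.0125 gives 88.2%.

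A standardized change effect of 0.84 is not far-fetched. If the group difference fell from 1.7 to 0.72 SD (both in Sample Size), the difference in change would be 0.98 SD. With equal SDs and an assumed within-person correlation of 0.32, the standardized effect is 0.98/√(2 × (1 − 0.32)) = 0.84. Both alphas are thus compatible with a figure of about 88%.

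**The case against.** **The split is legitimate.** Bonferroni over four named outcomes holds the family-wise error at 5%, and it permits a confirmatory claim on step latency, say, even if time to stabilization is null. The authors may want that: the Discussion would take either a longer time to stability or a longer step latency as evidence of impairment, and the Abstract speaks of the primary outcome in the plural. This stands as a reason why someone might choose the split. It does not remove the mismatch, because Outcome Measures is explicit that there is one primary outcome.

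**The cost is disclosed.** The alpha, the divisor, the four outcomes and the 74% are all printed, and the sample size and analysis sections agree. This stands in full: no reader is misled and the type I error is not inflated.

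**Aim 2 has other analyses.** Comparisons of change and a longitudinal GEE model with a group-by-assessment interaction are also planned. Moreover, a non-significant PostRTP test would not demonstrate recovery at 89% power either. The argument is therefore about the chance of missing a real deficit, not about proving recovery.

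**Stronger readings that the protocol does not support.** A reader might infer that the 88% for change was silently computed at an uncorrected 0.05, since d = 0.72 comes close at that level. The protocol gives no effect size for change, and another plausible input gives 88% at 0.0125, so the alpha cannot be established. A reader might also see a fault in aim 1 being left uncorrected. Sample Size attaches the correction to aim 2 only, and aim 1 has more than 99% planned power at 0.05, so nothing of consequence follows.

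**Conclusion.** The point holds as a cheap improvement that should be made, not as an error in the plan. The aim 2 alpha does not follow the protocol's own ranking of outcomes, and the mismatch takes power for the primary PostRTP test from 88.9% to 74.5%, below the customary 80%. The size rests on the protocol's own planning inputs: d = 0.72, 40 assessed per group and a two-sided two-sample t test. A smaller true effect or missing visits would lower both figures.

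On the 88% for change, the finding is only that its alpha and effect size are not stated beside it.

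**What to change.** Before group data are examined:

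1. In phase 1 Sample Size and Statistical Analysis (aim 2), test time to stabilization at PostRTP at two-sided 0.05. Test step latency, step length and clinical score at PostRTP by Holm at 0.05, and only if the primary test is significant.
2. Restate the PostRTP power as 89% (d = 0.72, 40 per group, two-sided 0.05).
3. If four co-primary outcomes are intended instead, keep 0.0125 and 74%, and amend Outcome Measures to say so.
4. Print the alpha and the effect size behind the 88% for change.

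**Cost.** Changes of wording only, with no extra athletes or visits. The real downside of item 1 is that a secondary outcome cannot support a confirmatory claim when time to stabilization is not significant; it could then be reported only as exploratory.
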